**Fig. 3 Fig3:**
[figure not shown]
TEAM UP study high-level components diagram and key data sources

**Table 2 Tab2:** Summary of concepts and instruments / measurements used to collect data

Concept Measured	Measures / Instrumentation	Source (Fig. 3)
Cumulative incidence of (new) PrUs for pre-intervention (baseline) period	Cumulative Incidence rate = [(# of residents with 1 or more new PrUs during a 1-month period) ÷ (# of NH residents with 3 or more day stay)] × 100; calculated monthly to establish baseline over the 12-month period before each NH intervention begins.	• MDS 3.0 • NH self-report • EMR data extract
Cumulative incidence of (new) PrUs for intervention period	Cumulative Incidence rate = [(# of residents with 1 or more new PrUs during intervention period) ÷ (# of residents participating in intervention for 3 or more days)] × 100; calculated for the full 4-week intervention period.	• MDS 3.0 • NH self-report • EMR data extract
Braden Scale©	The Braden scale is being used per protocol by participating NHs to assess resident risk for PrUs at intervention start and weekly thereafter.	• EMR data extract
Repositioning frequency	The scheduled duration of time for a resident’s pressure exposure as reflected by the 2-, 3-, or 4-h time interval at which the resident is repositioned; each NH will be randomly assigned to one of the study’s 3 arms and will use a single NH-wide repositioning frequency.	• PMS Central Server containing Monitoring Management Software
Recorded repositioning frequency	The actual time interval at which repositioning occurs, as documented by the Leaf sensor; recorded in clock time hours and minutes, 24 h per day, from start to end of resident’s participation in the 4-week intervention. Repositioning activities of residents will be captured using the Patient Monitoring System; Admission, Discharge, Transfer (ADT) feed from NHS to Monitoring System enables a match for Study ID# to resident movement, which is required for resident tracking in the event of room change, discharge/readmission, or other events.	• PMS Central Server containing Monitoring Management Software
Repositioning protocol adherence: % agreement	Percentage of agreement between scheduled repositioning frequency and repositioning frequency recorded by wireless sensor: [(scheduled clock time - recorded clock time = # minutes difference) ÷ 60] × 100]; calculated for each resident’s repositioning episode.	• PMS Central Server containing Monitoring Management Software
Medical Severity —Comprehensive Severity Index (CSI)	Calculated score on severity resulting from distillation of physiologic parameters, signs, symptoms, laboratory results, physical findings, and diagnoses, using the modified Comprehensive Severity Index (CSI), a risk adjustment system. The more abnormal the signs and symptoms, the higher the severity score: Level 1 is normal to mild, and Level 4 is catastrophic, life-threatening, or likely to result in organ failure. Individual components thought to influence a resident’s skin tolerance to pressure exposure will be monitored from assessment to assessment for Leaf, resident care parameters, CSI, and Braden score, with data extracted from EMR and the most recent MDS 3.0 assessment (initial, annual, quarterly, or change in status).	• MDS 3.0 • EMR data extract
Clinically assessed risk level (Braden Scale)	Total summed score (range 6 to 23) on the *Braden Scale for Predicting Pressure Sore Risk©*, comprised of 6 subscales (sensory perception, mobility, activity, moisture, nutrition, and friction & shear). Braden Score will be categorized as low (15–23), moderate (13–14), or high (10–12) risk. Collected weekly during intervention. Routinely collected by NH on admission, weekly × 4, quarterly, and upon suspected change in health condition. Change in category will be extracted.	• EMR data extract
Culture Assessment	Demographic & NCAT data will be used to assess the basic characteristics of participants and healthcare setting and clinical area worked. Data to be collected from each participant include, Length of time employed, job category, age, and gender.	• Qualtrics survey on iPads
Staff mix	The number of RNs, LPNs, and CNAs who work at each NH per day each day during the 4-week intervention at that NH, and for 12 months prior to intervention start.	• NH self-report
Staff turnover rate	[(Number of nursing staff (CNA, LPN, & RN) who leave during the time period) ÷ (Number of nursing staff at beginning + Number of nursing staff at the end ÷ 2)] × 100.	• NH self-report
Labor cost: 1) Training 2) Conducting repositions	1) Time needed for training nursing staff multiplied by respective wage & fringe rates of training participants, 2) number of repositioning’s for each NH and study arm and time to conduct repositioning collected by wireless sensor system; multiplied by nurse wage & fringe rate.	• NH self-report
Non-labor cost inputs	Market prices paid fully depreciated over their respective useful life will be used to calculate daily equipment cost rates. Includes VE surfaces, Leaf services, and sensor use.	• NH self-report

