##### Resident-level data.

Resident data extracted from the PM system database and the 12-month baseline and 4-week intervention MDS (batch file) and EMR; each resident will be assigned a study ID number prior to data extraction. New PrU incidence will be collected during the intervention period. Baseline data will be collected for 12 months just prior to intervention launch and will consist of EMR, MDS, and PrU incidence (Table 2) data. Intervention data extraction (of EMR, MDS, and PM system data) will occur weekly during the intervention 4-week period. The PM system will schedule resident repositioning frequency and gather resident repositioning sensor data automatically according to NH standards of care. Data collected by each resident’s sensor will be automatically communicated wirelessly through a proprietary mesh network of relay antennas to the respective NH’s Central Monitoring Station containing turn management software. Wireless sensor data on all monitored residents will be stored by the PM system. The wireless sensor number will become associated with a resident study identifier to be created as described below. The study ID number will be used to facilitate data comparisons. Wireless sensor data for all monitored residents will be securely stored in the PM system database.

Bench testing and clinical trials of the PM system’s wireless sensor have demonstrated it to be a valid measure of active and passive movement (repositioning). The sensor’s sensitivity accuracy is +/− 2.5% consistent with the industry standard for a linear triaxial accelerometer. Studies and clinical data show that the device effectively detects position changes according to threshold parameters, like degree or angle of position change. Wireless sensor data on all monitored residents will be securely stored in the patient monitoring system database. Wireless sensor data along with other resident data, including EMR data, will be transferred to the researchers for analysis. Turn management software in the PM system displays each resident’s repositioning history and current positional status in an organized and simple way on strategically placed nursing station and hallway display screens, making staff aware when resident repositioning actions are becoming necessary or are overdue. The percentage of on-time repositioning will be calculated for the period during which the wireless sensor is worn.

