##### EMR integration of patient monitoring system and CSI procedures.

The EMR will be used to facilitate data collection and export of study-related data, which includes an interface with wireless sensor data. This approach eliminates costly labor-intensive, in-person fidelity checks and minimizes research burden on staff. Individual wireless sensors will communicate with wireless antennas placed throughout the NH, permitting resident monitoring in all NH areas. The patient monitoring system will allow us to ascertain repositioning protocol adherence by measuring consistency between scheduled, performed, and documented repositioning frequency with random weekly observational repositioning checks to ensure repositioning fidelity. With CSI and other resident data, medical severity components will be assessed by staff based on NH policies and procedures and monitored in relation to risk level.

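### The Table 2 formula for repositioning adherence gives signed deviation as a percentage of one hour, not percent agreement: a turn exactly on schedule scores 0%.

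*Protocol article*

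**What the plan says.** In Table 2, the row on repositioning protocol adherence describes the measure as "Percentage of agreement between scheduled repositioning frequency and repositioning frequency recorded by wireless sensor". It gives the formula "scheduled clock time - recorded clock time = # minutes difference) ÷ 60] × 100", to be "calculated for each resident’s repositioning episode". It shows no absolute value, no subtraction from 100 and no rule for combining episodes.

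Other parts of the article bear on fidelity:

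- Table 2, row on repositioning frequency: the assigned exposure is "The scheduled duration of time for a resident’s pressure exposure as reflected by the 2-, 3-, or 4-h time interval at which the resident is" turned, that is 120, 180 or 240 minutes.
- Table 2, row on recorded repositioning frequency: the actual interval between turns, taken from the sensor in hours and minutes around the clock for the whole of a resident's participation.
- Resident-level data: "The percentage of on-time repositioning will be calculated for the period during which the wireless sensor is worn". No on-time window is stated.
- EMR integration of patient monitoring system and CSI procedures: adherence is to be ascertained by "measuring consistency between scheduled, performed, and documented repositioning frequency with random weekly observational repositioning checks to ensure repositioning fidelity".
- Treatment fidelity: the weekly observations check that the system detects turns correctly.

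None of these corrects the Table 2 formula.

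**The concern.** A percentage of agreement should be 100 when schedule and record coincide and should fall as they move apart. The printed expression is zero at perfect coincidence, reaches 100% for a turn a full hour early and becomes increasingly negative as a turn gets later. Anyone who reads the result by its label would rank episodes wrongly.

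Adherence carries weight in this trial. Under Statistical power, overlapping confidence intervals are taken to confirm no difference between arms. Arms that were not kept apart in practice would push towards that conclusion. Under Risk and challenges, the article itself says it must be able to show that repositioning took place at the assigned interval. Of the two percentage summaries of adherence in the article, this is the only one given a formula.

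**Working it through.** **Inputs.** The formula, its label and the per-episode unit come from the Table 2 adherence row. The assigned intervals T = 120, 180 and 240 minutes come from the Table 2 repositioning frequency row. The article reports no adherence value, so there is no figure to reproduce and the formula is evaluated directly.

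**Step 1: the printed formula.** Let d = scheduled minus recorded time in minutes, so d is positive for an early turn. The printed score is S = d / 60 × 100. The last two columns test whether a lost term at the front of the expression could rescue it.

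| Turn | d (min) | S as printed | 100 - S | 100 × (1 - abs(d)/60) |
|---|---|---|---|---|
| on time | 0 | 0% | 100% | 100% |
| 30 min early | +30 | +50% | 50% | 50% |
| 60 min early | +60 | +100% | 0% | 0% |
| 30 min late | -30 | -50% | 150% | 50% |
| 60 min late | -60 | -100% | 200% | 0% |
| 120 min late | -120 | -200% | 300% | -100% |

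S is zero at perfect agreement and unbounded. Restoring only a leading 100 minus term gives a turn 30 minutes late 100 - (-50) = 150% agreement. An absolute value is needed as well, and even then the score falls below zero once the deviation exceeds 60 minutes.

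**Step 2: what averaging would do, if it were done.**

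- One turn 60 minutes early and one 60 minutes late: signed mean (100 - 100)/2 = 0%, the same as two perfect turns. The mean absolute value is 100%.
- Four turns with deviations of 45 minutes each way and 30 minutes each way: scores ±75 and ±50, signed mean 0%, mean absolute value (75 + 75 + 50 + 50)/4 = 62.5%.

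**Step 3: an absolute, interval-scaled alternative.** A = 100 × max(0, 1 - abs(d)/T).

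| abs(d) | T = 120 | T = 180 | T = 240 |
|---|---|---|---|
| 0 | 100% | 100% | 100% |
| 30 | 75% | 83.3% | 87.5% |
| 60 | 50% | 66.7% | 75% |
| 120 | 0% | 33.3% | 50% |

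A is 100 at perfect agreement, cannot go below 0 and does not cancel under averaging.

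**Step 4: an on-time percentage on its own.** Suppose, as an assumption, that on time means turned by the due moment plus some grace. A home assigned 4 h but turning residents every 2 h would then score 100%. Its recorded intervals would show 120 minutes against 240, and A would be 100 × (1 - 120/240) = 50%.

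**The case against.** The strongest reply concerns reach, and most of it stands.

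- A reader might infer that the trial cannot assess fidelity, or that this score is the only protection against a null result from arms that were never separated. The article does not support that. The recorded interval, one row above in the same table, shows separation directly without this formula, and an on-time percentage is also planned.
- A reader might also infer that early and late turns do cancel. The score is defined per episode, nothing cancels within an episode, and no averaging rule is stated. The retained sign permits cancellation but does not compel it.
- Dividing by 60 minutes in every arm can be defended as a choice of scale, since 30 minutes late then means the same everywhere. Scaling by interval gives the 4-h arm a better score for the same lapse (87.5% against 75% in the 2-h arm). The fixed divisor alone is not an error.
- The printed brackets do not balance (one opening square bracket, two closing), which suggests a slip of notation rather than a deliberate method. That is plausible, but Step 1 shows that restoring a leading term alone does not repair the formula.
- The score is not named among the model predictors under Quantitative analyses, and it enters neither the pressure ulcer outcome nor the power calculation.

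The reply leaves the central fact untouched: the formula does not compute what its label says, and nothing else in the article corrects it. This is a misstated definition, not a detail left to a fuller document.

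**Conclusion.** The point holds for this one derived score. As printed, it is signed deviation as a percentage of one hour: 0% on time, +100% at 60 minutes early, -200% at 120 minutes late. This follows from the formula alone and rests on no assumption beyond reading it as written. Cancellation is conditional on signed values being averaged.

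The wider reading, that fidelity as a whole is unmeasurable, is not supported. The time stamps, recorded intervals and planned on-time percentage are intact, and the primary comparison and sample size do not depend on the score. It should be corrected before adherence is analysed, but it does not threaten the main result.

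**What to change.** Replace the Table 2 expression with a per-episode score on the absolute difference, for example A = 100 × max(0, 1 - abs(minutes difference) / assigned interval in minutes). If one common scale across arms is preferred, say so and keep a fixed divisor with the absolute value, the subtraction from 1 and the floor at zero.

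Report signed deviation in minutes separately, so that systematic earliness or lateness is visible. Show separation of the arms by the distribution of recorded intervals in each arm. If the on-time percentage under Resident-level data is also used, state its window and present it beside the recorded intervals, because alone it could count turns made far too early as adherent.

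This changes a measurement definition only and no care rule. It uses time stamps already stored, including those from the three homes where implementation is complete. The cost is a corrected table cell and a little recalculation.

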Current PrU prevention repositioning protocols (derived from two small 1962 studies [18]) recommend repositioning residents at moderate, high, and severe-risk every 2 h. With VE surfaces, it may be possible to reduce repositioning frequency by extending the repositioning interval (time elapsed between scheduled repositioning of residents) from 2 to 3 or even 4 h without an increase in PrU development. In the last decade, only two studies have examined repositioning protocols. One study reported fewer PrUs in residents using VE surfaces with a 4-h repositioning interval than in residents who used non-VE surfaces with more frequent repositioning [19, 20]. The second study, Turning for Ulcer ReductioN (TURN) trial, found no significant differences in PrU incidence between 2, 3, or 4-h repositioning intervals in a sample of moderate and high-risk residents using VE surfaces. In these two studies, 90% of all new PrUs occurred within the first 15 days [20]. However, new PrUs cannot be attributed to any single factor [21], and these analyses did not comprehensively examine changes in residents’ PrU risk levels or their physiological and disease factors (medical severity).

We will examine the effects of repositioning frequency (using assigned repositioning intervals of 2, 3, or 4 h) on residents at low, moderate, and high risk of developing PrUs (Braden Scale score 10-23) and will explore the effects of risk level and medical severity individually and in combination over a 4-week intervention period. Residents deemed to be at low risk are not commonly studied, but they too develop PrUs [2, 14–16] and are therefore included in this study. An FDA-cleared patient monitoring (PM) system using individual wireless tri-axial accelerometer sensors will record resident position and movement, automate repositioning schedules, provide visual cues to nursing staff [22] via electronic display screens at the nursing station and unit hallway(s) that indicate when each resident needs repositioning, and confirms completion of repositioning. This system provides a timestamp that repositioning occurred and addresses concerns about nursing electronic medical record (EMR) documentation compliance.

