The specific aims of the TEAM-UP (Turn Everyone And Move for Ulcer Prevention) study are to:Aim 1: Determine differences in the incidence of new pressure ulcers (PrU) in nursing home (NH) residents at low, moderate, and high risk using VE support surfaces and repositioned at intervals of 2, 3, or 4 h, in nine randomly assigned NHs over a 4-week period, using the patient monitoring (PM) system to determine movement.Aim 2: Determine how medical severity components (as measured by a modified Comprehensive Severity Index [23, 24]), changes in clinically assessed risk level (low, moderate, high as measured by the Braden Scale© [25]), assigned repositioning intervals, and their interactions are associated with development of PrUs, controlling for resident demographics.Exploratory Aim: Evaluate PrU prevention intervention approaches in NH groups repositioned at 2, 3, or 4-h by: 1) comparing the intervention resource costs (VE support surfaces, PM system service/sensor use, fixed and variable labor costs for training and repositioning) and incremental cost-effectiveness ratio of cost per % reduction in PrUs, and 2) exploring staff and resident satisfaction with intervention approach.

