## Methods

The TEAM-UP study is a cluster randomized clinical trial with facility-level use of an assigned repositioning interval as the primary intervention and will be conducted at 9 NHs that are all using VE support surfaces. Each participating NH will be randomly assigned to one of three intervention arms. Each arm will have 3 NHs with each NH using a single, NH-wide repositioning interval at either 2, 3, or 4 h as standard of care during the 4-week intervention period. Randomization will occur at the facility level. The sequence in which the repositioning intervals are to be implemented will be randomly ordered and, then assigned to NHs inclusive of each arm of NHs. Thus, 3 clusters of 3 NHs are created with randomly sequenced repositioning intervals.

A secondary cluster is created within each NH as the NH implements its standard risk assessment protocol; residents will be clinically categorized forming clusters by level of risk for developing a new PrU. Level of risk categorization into 3 groups is defined by a Braden score of low (15–18), moderate (13–14), or high (10–12) [32]. All eligible residents will wear a wireless triaxial accelerometer sensor throughout the intervention as part of the NH’s standard of care. Residents may refuse the sensor and can decline to move when prompted by staff as part of their right to refuse care (see Fig. 1). This pragmatic approach offers a unique opportunity to study a single NH-wide repositioning schedule, thus avoiding the potential for staff confusion associated with resident-level random assignment to repositioning intervals, which would require staff to simultaneously execute multiple turning schedules.

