#### Analysis

##### Quantitative analyses.

We hypothesize that there will be no significant difference in PrU incidence between the 3 treatment arms in the study using three risk level groups: high risk (Braden Scale Score, 10–12), moderate risk (Braden Scale Score, 13–14), and low risk (Braden Scores > 14). The hypothesis of no group difference will be tested by examining whether the 95% confidence intervals of the rates of PrU and the 2-h repositioning overlap. If so, the hypothesis for no group difference will be confirmed. We will also determine how changes in medical severity components (as measured by a modified Comprehensive Severity Index), change in clinically assessed risk level (low, moderate, high as measured by the Braden Scale) and their interactions with repositioning schedule are associated with PrU development.

Descriptive statistics will be used to examine resident status, interventions, outcomes, and cost elements. For categorical variables, we will create contingency tables and use chi-squared or Fisher’s exact tests to determine the significance of bivariate differences. For continuous variables, we will use analysis of variance or non-parametric tests, depending on variable distributions. A two-sided *p*-value < 0.05 will be statistically significant. Intervention cost by NH and study arm and incremental cost-effectiveness ratios (ICERs) will be calculated and compared for cost per percentage reduction in PrUs. Sensitivity analysis will be conducted with the range of observed repositioning times, nurse salaries, and market prices for non-labor inputs to assess the robustness of the ICERs and their sensitivity to labor and non-labor input prices.

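### Aim 2 measures change in risk level as a move between Braden categories of very unequal width, so one point counts as a change at two cut-points while any decline within the low band counts as none

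*Protocol article*

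**What the plan says.** Aim 2, in the Background's list of specific aims, asks how "changes in clinically assessed risk level (low, moderate, high as measured by the Braden Scale" and other factors, with their interactions, relate to ulcer development. The Quantitative analyses section repeats the predictor as "change in clinically assessed risk level (low, moderate, high as measured by the Braden Scale".

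Table 2, in the row on clinically assessed risk level, fixes the bands: "Braden Score will be categorized as low (15–23), moderate (13–14), or high (10–12) risk". It then says what is taken from the record: "Change in category will be extracted". Another row of Table 2 has the scale used "to assess resident risk for PrUs at intervention start and weekly thereafter". No section sets a minimum point change.

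The regression paragraph that follows enters risk level as a time-varying predictor, possibly lagged by one assessment, and includes interaction variables. Table 2 also says, in its medical severity row, that the Braden score is followed from assessment to assessment. Nowhere is change in that score named as the measure of change in risk.

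The article is not consistent about the low band. The Background gives the studied range as "Braden Scale score 10-23" and the analysis section has "low risk (Braden Scores > 14", both in line with Table 2. The Methods section has risk level "defined by a Braden score of low (15–18), moderate (13–14), or high (10–12".

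**The concern.** The three bands hold nine, two and three score values. A predictor defined by crossing between them does not measure the amount of change. It registers one point when the resident sits next to a cut-point, and nothing when a resident well inside the low band loses several points.

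Two things are at stake, both in Aim 2. First, decline among low-risk residents goes unseen until they cross below 15, although the Background presents their inclusion, and the tracking of fluctuating risk, as what this trial adds to earlier work. Second, both moderate scores, and the scores 12 and 15, lie one point from another band, so a single-point rating difference there is recorded as a change in risk. If such error is unrelated to ulcer development, it would tend to weaken both the coefficient for change in risk and its interaction with repositioning interval.

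**Working it through.** There is no figure in the plan to reproduce here. The check has two parts; only the second needs an assumption.

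**1. What the bands do, from Table 2 alone.** Inputs: integer scores 10–23; bands 15–23, 13–14 and 10–12.

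- There are 13 possible one-point falls. Two change category: 15 to 14 and 13 to 12. The other 11, including 14 to 13, do not.
- For a fall of d points there are 14 − d possible start–end pairs. For d of 3 or more only the low band can hold both ends, which gives 9 − d pairs with no category change.

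| Fall (points) | Possible pairs | No category change |
|---|---|---|
| 4 | 10 | 5 |
| 5 | 9 | 4 |
| 6 | 8 | 3 |
| 7 | 7 | 2 |
| 8 | 6 | 1 |
| 9 or more | 5 or fewer | 0 |

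The single 8-point case is 23 to 15. These are counts of possible pairs, not expected frequencies. With the low band of the Methods section, 15–18, the largest fall hidden within it is 18 − 15 = 3 points. The cut-points at 12/13 and 14/15 are the same under either version.

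**2. False changes from rating error.** Assumptions, none of them given in the documents:

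- the resident's true score is constant;
- there are five ratings (start plus four weekly);
- each rating is off by exactly one point with total probability e, split equally up and down;
- errors are independent between weeks.

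At a true score of 12, 13, 14 or 15, only one of the two one-point errors crosses a cut-point. Each rating therefore falls in the wrong category with probability q = e/2. The chance that five ratings do not all agree in category is

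1 − (1 − q)^5 − q^5.

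- e = 10%, q = 0.05: 1 − 0.7738 − 0.0000 = 0.226
- e = 20%, q = 0.10: 1 − 0.5905 − 0.0000 = 0.409
- e = 30%, q = 0.15: 1 − 0.4437 − 0.0001 = 0.556

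At a true score of 11, or of 16 or more under the Table 2 bands, a one-point error cannot change the category and the probability is 0. A score of 10 borders the severe range, which is excluded from analysis, and is left out of this range.

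**The case against.** The strongest reply is that the regression paragraph enters risk level as a time-varying level, which also carries differences between residents, and does not spell out how change is coded. That coding could sit in an analysis plan, and the Table 2 line could be read as a data-extraction note. This stands in part: the level term would retain information that a change indicator loses. But the aim, Table 2 and the analysis section all describe change in terms of the three categories, and none gives the total score that role.

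A reader might infer that the predictor would consist mostly of noise. The documents do not support that. The calculation above sets true change to zero, so it cannot say what share of observed changes would be false, and no attenuation or loss of power has been estimated. Larger rates follow from larger assumed error: a rounded normal error with SD 0.5 to 1.0 per rating gives 58–90% at scores 12–15. That, however, supposes that about 32–62% of ratings are wrong, and the documents give no reliability figure to justify it. Errors that persist from week to week would make false changes rarer than shown.

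The 8-point fall is also the extreme case: it is one pair of scores and depends on the 15–23 band.

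Finally, the categories are the trial's cited risk groups and are familiar to clinicians. That is a good reason to keep them for stratification and reporting, but not to make crossing between them the only measure of change.

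**Conclusion.** The concern holds for Aim 2. That one point suffices at 12/13 and 14/15, and that no decline within the low band counts, follows from the stated bands without any assumption. The largest hidden decline is 8 points under Table 2 and 3 points under the Methods section; the article must settle which band applies.

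The frequency of false change is conditional: about 23–56% over five ratings for a stable resident at 12–15 if 10–30% of ratings are off by one point independently, and 0 at 16 or more. How far this weakens the Aim 2 estimates cannot be derived from the documents. The Aim 1 comparison of ulcer incidence does not use change in risk level and is unaffected.

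**What to change.** In the Aim 2 model, replace category change with two terms from the weekly total Braden score: the baseline (or lagged) score, and the change in total score from it. Use the change term in the interaction with repositioning interval, and check linearity. Keep the three categories for the baseline stratum, and report category change as a secondary or descriptive result. Reconcile the low band in the Methods section with the Background, Table 2 and the analysis section.

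Do not require a category change to be confirmed at a later weekly score. A change first seen at week 1 would be confirmed only at week 2, and the Background reports that 90% of new ulcers in the two earlier studies arose within 15 days. Confirmation could therefore rest on information that comes after the ulcer.

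The cost is wording in the analysis plan; the scores are already collected. A per-point coefficient is less familiar than a category shift, and change in total score still carries some rating error.
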